**Acceptability of GP_Posit**		
Recruitment rate	Do eligible mothers consent to participate?	Number of eligible mothers/mothers who consent.
Attrition rate	What is the attrition rate?	Number of randomized mothers/mothers that are lost to follow-up.
**Other elements to consider**		
Contamination^a^	Do intervention mothers share content with other mothers?	Number of intervention mothers who shared content.
Co-intervention	Do mothers and/or infant participate in other research projects?	Number of mothers/infants participating in other research projects.

^a^Only for experimental group mothers

#### Other outcomes

The secondary objective of this pilot study is to estimate the preliminary effects of GP_Posit on mothers and preterm infant outcomes. Maternal outcomes include maternal sensitivity to cues and beliefs regarding their preterm infant’s needs and their own maternal role. Preterm infant outcomes include neurodevelopment.

Maternal sensitivity to cues is measured using the Parent-Child Interactions (PCI)–Feeding scale [9]. Mothers are videotaped while they feed their infant and this interaction is then coded, by a trained and certified study author who has been previously assessed for inter-rater reliability, using the 76 items of the PCI-Feeding scale. The 76 items are subdivided into four caregiver subscales (sensitivity to cues, response to distress, social-emotional growth fostering and cognitive growth fostering), and two infant subscales (clarity of cues and responsiveness to caregiver). Higher scores indicate a better sensitivity and mother-infant relationship [9]. Cronbach alphas vary from 0.6 to 0.88 and the PCI-Feeding scale has demonstrated great validity [9]. The PCI-Feeding scale has been used in at least six previous RCTs evaluating similar interventions, in the NICU, with parent-preterm infant dyads [20, 21, 23, 29, 33, 34]. Maternal beliefs about their preterm infant’s needs and their own maternal role is measured using the NICU: Parental Beliefs Scale (NICU:PBS) [56] at *t*_4_. The NICU: PBS is an auto-administered Likert type scale composed of 18 items and has a Cronbach of 0.75 to 0.91 [56].

The preterm infant’s neurodevelopment is assessed using the General Movement Assessment (GMA) tool [57] and electroencephalograms (EEG). The GMA is used to measure the quality of the newborn’s general movements repertoire [57]. A normal repertoire indicates normal neurodevelopment, and in case of neurological impairment the quality of general movements is lower. The GMA has been validated with a preterm infant population [58] and is also a valid indicator of cerebral palsy [59]. A 2-min video is taken while the infant is on its back, without any positioning aids. Videos will then be coded by a certified study author. The cerebral activity is assessed by an 8-probe portable EEG measuring resting state over a period of 30–40 min following which connectivity analyses will be performed.

#### Other confounding variables

Mother’s stress and anxiety as well as frequency of skin-to-skin contacts, parental presence at bedside and breastfeeding will be considered because of their potential to influence sensitivity [60]. The Parental Stressor Scale: Neonatal Intensive Care Unit (PSS : NICU) is used [61] to measure maternal stress. The PSS: NICU is an auto-administered Likert type scale composed of 50 items. It has been validated in a North-American context and has a Cronbach α of 0.89 to 0.94 [61]. To measure mother’s anxiety, the State-Trait Anxiety Inventory (STAI), an auto-administered questionnaire, has been selected [62]. The STAI is widely used in studies done with mothers of preterm infants in the NICU. It has been specifically developed to measure state and trait anxiety in adults with a Cronbach α of 0.93 [62]. Frequency and length of skin-to-skin contacts, frequency and length of parental presence at the infant’s bedside, and frequency of breastfeeding will be collected through medical chart review.

### Participant timeline

Mother-infant dyads are being enrolled during the first week after birth. Once informed consent is obtained, questionnaires in an opaque and sealable envelope are given to the mother to complete in the NICU room within the following 24-h after which they are sealed and collected by a member of the research team. Preterm infants also undergo the EEG, which is performed by the research team in the NICU individual room (−*t*_1_). When mothers are allocated to usual care, the nurse informs her that a member of the research team will meet with her when her infant reaches 36 WGA, or at time of discharge or transfer to another NICU, whichever occurs first. When mothers allocated to the experimental group, the intervention nurse plans the first intervention session based on the mother’s availabilities. The intervention goes on from that time until the preterm infant reaches 35 WGA (*t*_1_ through *t*_3_). To finish, a member of the research team meets with the mother when the infant reaches 36 WGA for data collection (*t*_4_). At this timepoint, the mother completes questionnaires, an EEG is performed to the preterm infant, a video of the preterm infant is taken for the GMA analysis and a feeding video is with the mother. If the preterm infant in not fully orally feeding at 36 WGA, the feeding video is done later, that being as soon as the infant is fully orally feeding. Full participant timeline is presented in Table 3.

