#### Secondary objective

The secondary objective is to estimate the preliminary effects of GP_Posit on mothers and preterm infants’ outcomes. The specific question leading this study is : what are the preliminary effects of the GP_Posit intervention, compared to standard care, at the primary endpoint (when preterm infants will have reached 36 weeks of gestational age (WGA)) on:
(Q1) Maternal sensitivity score to their preterm infant’s cues during oral feeding.(Q2) Maternal beliefs about their preterm infant’s needs and their maternal role in the NICU.(Q3) Preterm infant cerebral activity synchrony during eyes-closed electroencephalogram.(Q4) Preterm infant will have better quality of general movements.

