### Eligibility criteria

Mother-infant dyads are recruited in the GP_Posit trial as per the following criteria. Dyads are eligible to participate if the mother (1) speaks, writes, and reads French and/or English and (2) is 18 years or older, and the preterm infant(s) is/are (3) born between 27^0/7^ and 31^6/7^ WGA, as estimated by the medical team or antenatal ultrasound performed during the first trimester, and (4) expected to be hospitalized a minimum of 4 weeks in the NICU before being transferred in another center or obtaining their discharge. These criteria have been established in order to ensure that the mother-infant dyads will be in the NICU during an acceptable period of time to participate in the intervention if randomized in the experimental group. Moreover, preterm infants born before 27^0/7^ are not included as they only start to show behavioral stress and stability cues around 28 weeks of gestational age [48] and mothers in the experimental group will be guided to detect these behavioral cues.

Dyads are not eligible if the mother (5) uses illicit substances, (6) has an unstable mental health as evaluated by a NICU healthcare professional, such as a social worker or (7) gives her infant for adoption after birth. These conditions (5 and 6) could hamper parental competencies [49, 50]. Dyads will also not be eligible if the preterm infant(s) (8) requires surgery because their health condition might be too precarious to participate in the intervention, (9) has an intraventricular hemorrhage greater than grade II, (10) has a severe genetic condition associated with neurodevelopmental impairment or (11) receives opioids or anti-epileptic drugs because these conditions might affect infants’ behavioral activity.

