##### Experimental intervention structure

The intervention is being provided by two neonatal registered nurses who have been trained to implement the experimental protocol. However, the same nurse always meets with the same mothers throughout the intervention. The intervention takes place at the infant’s bedside where one intervention nurse meets with the mother face to face. The intervention always takes place once a week, but the day of the week when intervention takes place depends on mother’s availabilities. The sessions start from the first week after birth to the last week before discharge or transfer to another center, or when the infant reaches 35 weeks of gestational age, whichever occurs first. It is planned that these sessions each last 30 to 45 min. During these weekly sessions, intervention nurses are demonstrating and then coaching mothers in performing the care giving activities, while always interpreting the infant’s cues and encouraging communication within the mother-infant dyad. Fathers are invited to be present during the intervention sessions, but their presence was not mandatory to be eligible to participate in the study.

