### Outcomes and data collection

Data collection starts following enrolment and consent. Data collection is performed by a member of the research team at different end points: before randomization (−*t*_1_), throughout intervention delivery (*t*_1_ through *t*_3_), and after the intervention that being when the infant reaches 36 WGA (*t*_4_).

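### The end-point visit (t4) is timed inconsistently: an early-departure alternative is written only for usual-care dyads, and no rule covers experimental dyads who leave before 36 WGA

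*Protocol article*

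**What the plan says.** Four places in the protocol article time the end-point visit.

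- **Secondary objective:** the effects are to be estimated "at the primary endpoint (when preterm infants will have reached 36 weeks of gestational age (WGA"). No exception is given.
- **Outcomes and data collection:** t4 falls "after the intervention that being when the infant reaches 36 WGA". No exception is given.
- **Participant timeline, usual-care sentence:** the mother is told that the meeting will be "when her infant reaches 36 WGA, or at time of discharge or transfer to another NICU, whichever occurs first".
- **Participant timeline, closing sentence, directly after the experimental-arm text:** "a member of the research team meets with the mother when the infant reaches 36 WGA for data collection". No exception is given.

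The questionnaires, the EEG, the general-movements video and the feeding video all belong to this visit. Only the feeding video has its own exception: for an infant not yet feeding fully by mouth at 36 WGA, "the feeding video is done later, that being as soon as the infant is fully orally feeding".

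Two other sections show that departure before 36 WGA is expected in either arm. Eligibility criteria ask only for an expected stay of at least 4 weeks before transfer or discharge. Experimental intervention structure ends the sessions in the "last week before discharge or transfer to another center, or when the infant reaches 35 weeks of gestational age, whichever occurs first". That is a rule for the sessions. It does not say when, or whether, t4 takes place for an experimental dyad that has left.

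**The concern.** If the timeline is followed as written, a control dyad that leaves early is assessed on leaving. An experimental dyad that leaves on the same day is either assessed later, at 36 WGA, or not assessed. That difference arises after allocation, so randomisation does not balance it.

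Three things could then differ by arm: the infant's age at assessment, the time between baseline and t4, and the proportion of dyads with no t4 data. Data analysis compares the arms by Cohen's d for sensitivity and beliefs, by a difference in proportions for general movements, and by Cohen's d on change from baseline for stress and anxiety. It states no adjustment for age at assessment. Unequal follow-up enters the change scores directly.

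The primary objective is touched as well. Table 1 counts the share of data collection carried out as planned and the dyads lost to follow-up. With two timing rules, it is not determined whether an assessment at transfer was as planned, or whether a dyad that left before 36 WGA is lost.

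**Working it through.** The plan gives no figure for age at assessment, so there is none to reproduce. The check is date arithmetic on the plan's own limits.

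**Inputs**
- Gestational age at birth: "born between 27^0/7^ and 31^6/7^ WGA" (Eligibility criteria).
- Expected minimum stay: 4 weeks (Eligibility criteria).
- Nominal t4: 36+0 (Secondary objective; Outcomes and data collection).
- Control alternative: discharge or transfer, if earlier (Participant timeline).

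**Formula**

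Age at departure = gestational age at birth + 4 weeks. Gap = 36+0 minus age at departure.

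| Born | Leaves at (4 weeks from birth) | Gap to 36+0 |
|---|---|---|
| 27+0 | 31+0 | 35 days |
| 28+0 | 32+0 | 28 days |
| 29+0 | 33+0 | 21 days |
| 30+0 | 34+0 | 14 days |
| 31+0 | 35+0 | 7 days |
| 31+6 | 35+6 | 1 day |

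If the 4 weeks are counted from the end of the first week of life, each departure is 7 days later. The gap is then 28 days at 27+0 and zero from 31+0 onwards. The 4 weeks are an expectation at enrolment, so 5 weeks is the largest gap only if that expectation is met.

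**Follow-up for the change scores.** Counted from birth, an infant born at 27+0 reaches 36+0 after 9 weeks but departs after 4. Baseline is taken around the first week in both arms, so the interval for the stress and anxiety change could differ by up to the same 5 weeks.

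**Can a bias be sized?** The shift in a mean would be roughly p × w × b, where p is the proportion of controls assessed early, w the mean number of weeks early, and b the change in the outcome per week in SD. The documents give none of the three. On assumed ranges:
- low: 0.10 × 1 × 0.1 = 0.01 SD
- middle: 0.20 × 2 × 0.2 = 0.08 SD
- high: 0.50 × 5 × 0.3 = 0.75 SD

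The high end is a corner case, because a mean of 5 weeks early needs every early leaver to have been born at 27+0. The formula also supposes that every early-leaving experimental dyad is assessed at 36 WGA. If they are missed instead, the mechanism is selective loss and the formula does not apply. A range of 0.01 to 0.75 SD shows only that the size is undetermined.

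**Precision for comparison.** With 10 per arm, the 95% CI half-width for d near zero is about 1.96 × √(2/10) = 0.88.

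**The case against.** The strongest reply is that this is a drafting slip and no arm-specific rule was intended. The usual-care sentence reports what a nurse tells a mother after allocation. The t4 definition under Outcomes and data collection does not distinguish arms. The closing sentence of the timeline introduces the only list of t4 assessments there, so it probably covers both arms. Table 3, which holds the full timeline, is not shown and may settle the matter. All of this stands as an argument against reading the text as a deliberate design. It does not remove the conflict: if the closing sentence covers both arms, it contradicts the usual-care sentence, and the same reconciliation is needed.

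A reader might also infer a bias of definite size in favour of GP_Posit. For instance, 30% of controls leaving 2 weeks early, with 0.2 to 0.4 SD of maturation per week, would give 0.12 to 0.24 SD. The documents do not support this. All three inputs are assumed. General movements are analysed as normal or abnormal, so an SD shift does not apply directly. The EEG connectivity analysis is exploratory and has no stated direction, and none is shown for stress, anxiety or beliefs.

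Nor is the feeding-video deferral a further difference between arms. It applies to both and ties the video to feeding readiness, which makes the sensitivity outcome less exposed to age. What remains is narrower: the exception is written for infants still short of full oral feeding at 36 WGA and does not cover a dyad that leaves before then.

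Finally, the effect outcomes are secondary and descriptive, no significance test is planned, and the CI half-width of about 0.88 is wide. This limits the severity and is accepted.

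**Conclusion.** The inconsistency is on the page and should be resolved; its severity is moderate. The early-departure alternative appears for usual care only, three other statements give 36 WGA alone, and early-leaving experimental dyads have no t4 rule although their departure is foreseen.

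On the plan's own limits and a literal reading, controls could be assessed up to 5 weeks before 36+0, falling to a week or less for births at 31 weeks. That rests on departure at the expected minimum of 4 weeks counted from birth. How often it would happen is unknown, because no discharge or transfer rates are given.

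The supported conclusion is that age at assessment, follow-up length and missingness could differ by arm. The documents do not show that they will, nor by how much or in whose favour. Beyond the effect estimates, the feasibility indicator on data collection performed as planned needs a single t4 rule to be countable.

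**What to change.** 1. Reconcile the Secondary objective, Outcomes and data collection, and Participant timeline (with Table 3 if it differs) to one t4 rule, in the same words for both arms. The first two already agree and need rewording only if the departure alternative is adopted.
2. Make the rule cover dyads that leave before 36 WGA and dyads that leave before full oral feeding, again identically in both arms.
3. Record the infant's postmenstrual age at each t4 assessment: questionnaires, general-movements video, EEG and feeding video.
4. Report that age, and the number of missing assessments of each kind, by arm.

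The cost is wording and one recorded date per assessment, in a trial described as still ongoing. Either choice has a modest downside. If assessment at departure is allowed, assessment age will vary within both arms. If the rule is 36 WGA only, some departed dyads will be counted as missing unless they are seen elsewhere, which would take extra effort.

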**Table 3 Tab3:**
[figure not shown]
Enrolment, allocation, intervention, and data collection

### Sample size

A convenience sample of 20 mother-infant dyads will be recruited. It has been suggested that a minimum of 10 participants per group is sufficient for pilot studies [63, 64]. A maximum of 24 dyads could be recruited in case of attrition which is anticipated to be around 20% based on similar intervention studies [20, 31, 34, 35].

### Recruitment

The NICU’s research nurse presents the GP_Posit trial to each eligible mother within 1 week after having given birth. After the project has been presented, mothers can ask questions, take all the time they need to read the information form, before consenting to participate. Recruitment occurs in the postpartum unit if the mother is still hospitalized or in their preterm infant’s single NICU room.

### Randomization and allocation

An independent biostatistician of the Applied Clinical Research Unit (Unité de Recherche Clinique Appliquée (URCA)) verified the sequence of randomization as per a computer-generated random listing of interventions applying a permuted block design with random blocks of two and four. Opaque, sealed, and sequentially numbered envelopes were prepared by a professional independent from the study team. Mothers consenting to participate in the trial are randomly assigned, in a 1:1 allocation ratio, to receive either the experimental intervention or usual care. Mothers uncover their allocated group by opening the envelope in presence of the intervention nurse.

### Blinding

Due to the nature of the intervention, it is not be possible to prevent mothers and intervention nurses of knowing the dyad’s allocated group since no mock intervention is offered to the control group. Nevertheless, the research team is blinded to the mother-infant dyads’ group. Video coders will also be blinded to the dyads’ group allocation.

### Data management

An identification number is being assigned to each dyad to preserve confidentiality. All data collected will be manually entered into an electronic database statistical software, and the original questionnaires will be kept under lock and key in the principal investigator’s office at the Université de Montréal. Data entry and coding will be performed by the same person. A verification will be done by a second person to compare with the original questionnaires. Files will be maintained in storage for a period of minimum 7 years after completion of the study, according to the center’s ethical board regulation.

### Feasibility criteria

The primary criteria for assessing feasibility will be based on adhesion to the intervention which is defined as mothers participating in at least four intervention sessions with the intervention nurse. To determine feasibility of the intervention based on adhesion, at least 80% of mothers will need to have participated to a minimum of four sessions.

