**Acceptability of design**		
Recruitment	Do the eligible mothers accept to participate?	% of eligible mothers that participate.
Randomisation	Do the mothers accept to be randomized?	Reason of refusal.
Data collection	Is it acceptable for mothers that we perform EEGs to their preterm infant?	80% of mothers accept.
	Is it acceptable for mothers that we perform the GMA to their preterm infant?	80% of mothers accept.
	Is it acceptable for mothers to be filmed while they breastfeed or bottle-feed?	80% of mothers accept.
	Is it acceptable for mothers to complete questionnaires?	80% of mothers accept.
General acceptability of the intervention^a^	Is it acceptable for mothers to participate in their infant’s positioning?	80% of mothers find it acceptable.
	Is it acceptable for mothers to participate in 30–45 min. intervention sessions, once to twice per week, throughout the hospitalization?	80% of mothers find it acceptable.
Appreciation^a^	Were mothers satisfied by the intervention?	80% of mothers were satisfied.
	Did mothers find it easy to participate?	80% of mothers found it easy.
	Did mothers find it challenging to participate?	Challenges encountered.
	Did the mothers find the intervention useful?	80% of mothers found it useful.
Retention^a^	Which strategies could enhance retention?	Suggested strategies by mothers.

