### Protocol amendments

Since the beginning of this pilot study in late 2018, protocol amendments have been done following challenges encountered regarding recruitment. We had originally targeted a sample size of 30 (15 dyads per group) based on Julious [66] with a planned recruitment rate of two to three dyads per week. However, we initially had a recruitment rate of one dyad per month which was sub-optimal. Our solution to optimize recruitment was twofold. First, we lowered the sample size to 20 (10 dyads per group) because this sample size allowed us to estimate feasibility and acceptability. Moreover, as suggested by Leon, Davis [67], pilot studies’ sample size should be based on pragmatics such as patient flow. Second, we also made a change in inclusion criteria as we included preterm infant born between 27^0/7^ and 31^6/7^ as opposed to originally planned 28^0/7^ to 31^6/7^ WGA. Since we observed that the time needed between −*t*_1_ and *t*_1_ was of at least 1 week, preterm infants born at 27^0/7^ WGA could participate as they would be 28^0/7^ WGA by the time the experimental intervention would start.

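### The four-session adhesion criterion does not fit the protocol's own session window for late-born infants, so failing it could reflect gestational-age mix rather than mothers' adherence.

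*Protocol article*

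**What the plan says.** Under Feasibility criteria, the protocol article defines adhesion as attending at least four sessions and requires that "at least 80% of mothers will need to have participated to a minimum of four sessions". It calls this the primary criterion for assessing feasibility. The count does not depend on gestational age at birth or on how many sessions a dyad could have had.

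The window for those sessions is set elsewhere:

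- **Eligibility criteria:** infants "born between 27^0/7^ and 31^6/7^ WGA" and "expected to be hospitalized a minimum of 4 weeks in the NICU".
- **Experimental intervention structure:** "The intervention always takes place once a week", on a day that suits the mother. "The sessions start from the first week after birth", and they end at discharge or transfer, "or when the infant reaches 35 weeks of gestational age, whichever occurs first". Participant timeline repeats the 35 WGA stop.
- **Participant timeline:** enrolment falls in the first week after birth. Questionnaires and a baseline EEG come before allocation.
- **Protocol amendments:** the time observed between baseline and the first session "was of at least 1 week".
- **Table 2 (Acceptability of design):** mothers are asked about sessions "once to twice per week, throughout the hospitalization", a different frequency from the intervention section.

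**The concern.** The criterion is a fixed count, but the window in which sessions can be given shrinks with gestational age at birth. An infant born at 27 0/7 has about eight weeks until 35 WGA; one born at 31 6/7 has just over three. If the window holds fewer than four weekly sessions, the mother fails the criterion whatever she does.

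This criterion serves the primary objective, and the pilot is meant to guide a large-scale trial. A result below 80% could mean that mothers did not come, or that many infants were born late in the eligible range. The first would call for a look at the intervention and the second at the design, and the rule as written cannot tell them apart.

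**Working it through.** **Inputs.** Eligible birth is 27 0/7 to 31 6/7, that is days 189 to 223, or 35 possible birth days (Eligibility criteria). The stop is on reaching 35 0/7, day 245 (Experimental intervention structure). Spacing is taken as 7 days. Enrolment is on day 0 to 7 of life (Participant timeline), and the first session comes at least 7 days after baseline (Protocol amendments), so it falls on about day 7 to 14 of life, or later. The experimental arm has 10 mothers (Sample size: 20 dyads, 1:1).

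**The plan's own figure.** Protocol amendments says that an infant born at 27 0/7 would be 28 0/7 when the intervention starts. 189 + 7 = 196 days = 28 0/7, which agrees.

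**Sessions available.** With birth day b and first session at age t days:

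sessions = floor((245 − b − t)/7) + 1

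| Born | First session day 7 | First session day 14 |
|---|---|---|
| 27 0/7 (189) | 8 | 7 |
| 30 0/7 (210) | 5 | 4 |
| 31 0/7 (217) | 4 | 3 |
| 31 6/7 (223) | 3 | 2 |

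For 31 6/7, day 7: (245 − 223 − 7)/7 = 15/7, floor 2, plus 1 = 3. A day-8 start also gives 3. From day 9 it is 2.

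**Who can reach four.** Four sessions span 21 days, so 245 − b − t ≥ 21, or b ≤ 224 − t.

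- Day 7: b ≤ 217, born at or before 31 0/7. Excluded: 6 of 35 birth days = 17%.
- Day 14: b ≤ 210, born at or before 30 0/7. Excluded: 13 of 35 = 37%.

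**Chance of meeting the 80% rule with perfect attendance.** Assume births are even over the range, and let X ~ Bin(10, p) with at least 8 of 10 needed.

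- Day 7: p = 29/35 = 0.829, P = 76%.
- Day 14: p = 22/35 = 0.629, P = 22%.

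**Sensitivity.**

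- *35 WGA read as through 35 6/7 (day 251).* The limit becomes b ≤ 230 − t. Day 7 excludes none (P = 100%). Day 14 excludes 7 of 35 = 20% (p = 0.80, P = 68%).
- *First session on day 0 or 1.* No birth day is excluded.
- *Births rising two- to threefold across the range (assumed).* Excluded: 23% to 26% (day 7) or 46% to 51% (day 14). The expected proportion able to reach four is then below 80%.
- *Twelve mothers (the maximum of 24 dyads), 10 of 12 needed, even births, stop at 35 0/7.* P = 66% (day 7) or 12% (day 14).
- *Twice-weekly sessions, about 3.5 days apart.* Born 31 6/7: five from day 7, three from day 14.

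**The case against.** The strongest reply is that the shortfall depends on how the schedule is read. The intervention section puts the start in the first week after birth, and a first session on day 0 or 1 makes four sessions possible for everyone. Consent, questionnaires and a baseline EEG come first, however, and the protocol's own experience is a delay of at least a week. The text also says once a week without fixing 7 days. With one session per calendar week, an infant born at 31 6/7 and first seen on day 7 could have a fourth session on day 22, exactly 35 0/7. That edge case stands, so the result should be stated for spacing of about 7 days. Table 2's higher frequency would also ease the problem, but it conflicts with the intervention section.

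A second reply is that an absolute count is a legitimate test of dose: if eligible dyads lack time for four sessions, that is a real feasibility finding. This is fair, and is why the count should still be reported. But the criterion is labelled adhesion, and Table 1 lists feasibility of the dose as a separate question.

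Three stronger readings are tempting and not supported:

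- *The 80% rule cannot be met.* It is a rule for the group, and whether it can be met depends on the gestational-age mix and the start day.
- *The four-week minimum stay leaves room for only three sessions.* From day 7, sessions on days 7, 14, 21 and 28 make four. The stay does not rescue late-born infants either, because those born after 31 0/7 reach 35 0/7 before day 28.
- *This is the only go/no-go rule for the primary objective.* The protocol never calls it that, and Table 2 sets other 80% thresholds, though for acceptability.

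**Conclusion.** The point holds in a limited form. On the plain reading (weekly sessions about 7 days apart, a stop on reaching 35 0/7, a first session on day 7 to 14), an infant born at 31 6/7 has two or three sessions available, and full attendance is scored as non-adherence. With births even over the range, 17% to 37% of dyads are affected and the chance of passing with perfect attendance is 76% down to 22%. Reading the stop as through 35 6/7 reduces this to 0% to 20% and 100% to 68%. The protocol does not give the birth distribution, so these figures are illustrations. Attrition, anticipated at around 20%, and early transfer are not included and could only lower the chance of passing.

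The protocol should fix this, but it does not invalidate the pilot. The defect is that the criterion mixes adherence with the length of the window.

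**What to change.** Leave the schedule as it is and separate the two questions.

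1. **Adhesion.** Count a mother as adherent if she attended the smaller of four and the number of weekly sessions available between her dyad's actual first session and its stop point. Keep the 80%-of-mothers threshold, with all mothers randomised to GP_Posit as the denominator. A mother who never starts should count as non-adherent, with the reason logged.
2. **Design feasibility.** Report separately the number and proportion of dyads for whom four sessions were available, together with the unadjusted count of mothers who attended four or more.
3. **Reconciliation.** Experimental intervention structure, Table 2, Participant timeline and Protocol amendments must be brought into agreement on when sessions start and how often they occur. Which version is right is for the investigators to decide.

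The smaller-of-four rule leaves the criterion unchanged for every dyad with four or more sessions available. Requiring a set percentage, such as 80% of available sessions, would change it for everyone: it demands full attendance at two to four sessions and allows one miss at five to eight. The proposed rule also demands full attendance when two to four are available, so sessions attended and available should be listed for each dyad.

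The cost is a short amendment and one extra tally in the feasibility logbook, which is already kept. Gestational age at birth is already collected. The downside is that adhesion no longer guarantees an exposure of four sessions, which is why the absolute count in item 2 must stay.
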